## Abstract

**Background:**

New methods are needed for collecting data of in- and outpatients and for improving outpatient compliance after discharge. Mobile technologies, such as smartphone apps, have shown promising results, (eg, helping unwell people by offering support and resources). Screening for the condition, including comorbidities, is a vital part of psychiatric care. Comorbid conditions, especially in emergency evaluation, are often missed, leading to inaccurate diagnosis and treatment. One way of improving diagnostic accuracy is to use a structured diagnostic process. Digitalized screening and follow-up have the advantage of making administration and scoring easier and less time consuming, thereby increasing response rate. To address these problems, we decided to create a smartphone app called The Blue App. The Blue App was developed through 6 steps, described in the manuscript.

**Objective:**

The aim of this paper is to describe (1) the development of The Blue App and (2) 2 planned research studies to evaluate the app.

**Methods:**

Two studies will be performed. Study 1 has a descriptive design, mapping comorbidities before and after the introduction of The Blue App. Study 2 has a randomized controlled design, measuring compliance with outpatient treatments as well as depressive symptoms, rated as changes in Montgomery-Åsberg Depression Scale scores during a 1-year follow-up.

**Results:**

We have described app development. Data collection for Study 1 started in autumn 2017. Study 2 will start in autumn 2018. We expect to have enrolled the 150 patients in Study 2 by December 2019. Final results will be published in a scientific journal.

**Conclusions:**

A technically advanced and easy-to-use Web-based mobile phone app corresponding to the unit’s needs was developed, and 2 studies are planned to evaluate its usefulness.

**International Registered Report Identifier (IRRID):**

RR1-10.2196/10121

## Introduction

Emergency units with 24/7 evaluation and admission facilities are important services for stabilizing adolescents with mental health crisis [1,2]. On admission to a unit, patients often need extensive mental health resources [3]. Demand for health production is high in emergency units when inpatient stays are short [4].

The largest intervention effect is reached during the first week of admission [5]. Short inpatient stays for acute stabilization are a challenge when it comes to structured diagnostic screening. Despite the availability of validated diagnostic screening instruments, pen-and-paper versions lead to poor response rates and consume resources, making their use less attractive [6]. The current toolbox is outdated for use in our population of adolescents, and new methods are needed for inpatient data collection and for improving outpatient compliance. Mobile technologies, such as smartphone apps, have shown promising results in terms of data collection and as an intervention for behavioral change, but little empirical evidence has been found to date [7,8].

Literature in the field of child and adolescent psychiatric inpatient emergency care is scarce, and studies are limited to characteristics of admitted patients [3]. Therefore, little is known about the course of illness after discharge. In Sweden, there has been no comprehensive evaluation and follow-up of children and adolescents admitted and discharged from psychiatric emergency units.

Diagnosing the condition and screening for comorbidity using validated instruments is a vital part of psychiatric care. Moreover, a structured screening procedure is also perceived as positive and valid by patients and their parents [9].

In psychiatric care, diagnostic interrater reliability among clinicians is weak [10]. Comorbid conditions are commonly missed during psychiatric evaluations, leading to inaccurate diagnosis and treatment. One way of increasing diagnostic accuracy is to use a structured diagnostic process, involving diagnostic screening instruments [11].

Digitalized screening and follow-up make administration and scoring easier and less time consuming for patients, parents, and staff. This helps increase the frequency of completed systematic psychiatric screenings. It also has the advantage of availability, as questionnaires can be sent to and answered on patients’ smartphones, increasing response rates [6]. This structured data collection would enable studies of child and adolescent psychiatric emergency inpatients in further research.

Apps have proved effective in helping unwell people, by offering support, resources, and information [7]. In recent years, several new smartphone-based solutions have been developed for mental health in general and specifically for child and adolescent psychiatry [12-16]. However, apps developed by health care professionals for adolescents must be innovative, useful, and fun to compete with apps not encouraging healthy behaviors [7].

To address these problems, we decided to create a smartphone app: The Blue App (referring to blue as the color of hope, as well as expressing moodiness). The Blue App is a Web-based tool made to resemble and function as a mobile app.

The aim of this paper is to describe the development of The Blue App and to present 2 research protocols aimed at evaluating the app.

## Methods

### Development of The Blue App

The process of developing The Blue App, from concept to working product, was divided into 6 steps.

#### Step 1. Identifying the Need for Quick and Easy Information Gathering

Since 2010, members of our group have introduced and developed interactive voice response (IVR) into Swedish child and adolescent psychiatry. This is a technology in which a server is programmed to use scripts in interaction with the user on their cell phone [9,14]. Johansson et al [17] have shown that emergency patients had their own cell phones and that the response rate among participating patients (N=60) was promising as each individual responded on average 91% (365/402) of their calls. An answering frequency of 100% was shown by 71% (30/42).

Our work with IVR inspired us to further develop technology to meet the unit’s needs regarding improved methods for the diagnostic and follow-up processes. In 2013, we published our first IVR paper [17]. Simultaneously, we were discussing the shortcomings at the unit regarding the identification of comorbidities. We were also discussing the development of a more sophisticated follow-up tool that would provide feedback using a visual presentation of changes in symptoms over time. At the same time, smartphones were becoming more common among adolescents. This enabled us to integrate our previous work with our efforts to widen the use of screening questionnaires in a better package than the older cell phones could offer.

To address the issues related to short inpatient stays and need for improved diagnostic screening, we decided to create a smartphone app based on our previous work.

#### Step 2. Identifying Desired Information and Choosing Adequate Screening Questionnaires

In addition to clinical evaluations, we wanted to screen for and describe the psychiatric conditions that were most frequently presented at emergency units. The most common reasons for admission to the unit were suicidal ideation, severely depressed mood, and acute crises. Our experience corresponds well with literature on child and adolescent psychiatry with regard to frequent comorbid states [2]. We also wanted to map changes in symptom severity before and after admission.

The validated screening questionnaires were chosen in collaboration with national key opinion leaders and with regard to frequent comorbid states in child and adolescent psychiatry [18-20].

The following 10 questionnaires were chosen:

Montgomery-Åsberg Depression Scale (MADRS-S): a 9-item diagnostic self-rating questionnaire measuring depressive symptoms during the previous 3 days [21]Mini International Neuropsychiatric Interview for Children and Adolescents (MINI-KID): a semi structured diagnostic interview concerning the core psychiatric disorders among children and adolescents [22]Alcohol Use Disorders Identification Test-Consumption: a 3-item screening questionnaire regarding alcohol use [23]Drug Use Disorders Identification Test: an 11-item screening questionnaire regarding drug use [24]Hopkins Symptom Checklist-10: a symptom inventory that measures signs of anxiety and depression [25]Sheehan Disability Scale: a scale assessing functional impairment in domains of work or school, social, and family life [26]Autism Spectrum Screening Questionnaire: a 27-item checklist that assesses symptoms characteristics of high-functioning autism spectrum disorder [27]Swanson Nolan and Pelham Questionnaire: a 30-item questionnaire assessing attention-deficit/hyperactivity disorder symptoms and behavioral problems [28]Deliberate Self-Harm Inventory-9: a scale showing the frequency of different ways of self-harming [29]Treatment Satisfaction Scale 2: a 6-item measure of treatment effectiveness [30] (included to evaluate the satisfaction of treatment but not a part of the research protocols)

#### Step 3. Examining the Feasibility in an Emergency Psychiatric Unit: Pilot Study

To evaluate the feasibility of the screening procedure, a pilot study was performed with adolescents admitted to the psychiatric emergency unit. The first aim was to assess the feasibility of administration of 10 questionnaires in a small consecutive population. The second aim was to learn more about the clinical relevance of the systematic screening, that is, would the results indicate more comorbidities than found in the medical records? Patients admitted to the unit between February 11, 2014, and March 14, 2014, were invited to participate and complete the 10 questionnaires regarding psychiatric morbidity and comorbidity to be included in The Blue App. All screening questionnaires involved using pen and paper.

We included 16 patients (12 girls and 4 boys; age: mean 15.6 (SD 1.31) years). Of these, 12 completed all the pen-and-paper screening questionnaires, whereas 4 patients could not complete their screening procedures due to early discharge. Of 10, 9 diagnoses at discharge were confirmed using MINI-KID. MINI-KID also identified, on average, 5 diagnostic areas of potential psychiatric interest, including the hazardous use of alcohol or substance abuse, none of which had been clearly addressed during the inpatient stay or mentioned in the psychiatric records.

#### Step 4. Getting Organizational Acceptance: Feasibility Study

The next step was to secure a way forward for The Blue App. As our aim was to use the tool in daily clinical practice, we decided to apply for funding from the funding body for all public psychiatric health care in Scania, South Sweden. All potential new procedures in Swedish public health care require a thorough assessment procedure to clarify the cost-benefit ratio, safety, and potential risks (feasibility study). The aim of this feasibility study was to clarify the requirements of The Blue App and to elucidate the cost-benefit and safety aspects so as to generate a basis for decision making for the funding body. Another part of the feasibility study was to collect knowledge about alternative solutions allowing the same functionality by investigating if comparable products were available on the market.

The feasibility study included about 15 meetings with the IT and finance departments. Clinicians’ needs were highlighted, which resulted in a thorough description of the technical requirements for 90 user cases, including mock-ups, flowcharts, and wireframes. The study concluded that no existing solution was available on the market. The final document was presented to the funding board with the working title “The Blue App.” The board approved funding in May 2015.

#### Step 5. App Construction

After approval, the next step was to call for public procurement using the feasibility study documents. In total, 3 tenders were considered, and representatives from each company were interviewed. The clinicians working on The Blue App were involved in decision making. Work with the company chosen, Stretch Öresund, proceeded with workshop sessions, creating a shared language and translating clinicians’ needs to the mindset of app architects. The work continued with meetings being held every 2nd week for a 6-month period, during which mutual feedback on the progress of The Blue App was given. The company’s CEO met with the unit staff to demonstrate the app and collect feedback to increase the chance of successful implementation.

The work resulted in an app corresponding with the unit’s needs. The structure of the development process, with frequent and regular meetings, was necessary to avoid misunderstandings. The development process allowed the app architects to gain a profound understanding of psychiatric care and to adapt solutions to the unit’s requirements.

#### Step 6. Workshop With Adolescents: What Do the Patients Think?

During the development of The Blue App, feedback was obtained through a workshop with adolescent end users. The main aim was to assess the user-friendliness of the app. We arranged the workshop in spring 2016, during which 10 adolescents, 5 boys and 5 girls aged 14-17 years, participated. Of these, 2 adolescents were undergoing psychiatric outpatient treatment. The participating adolescents were introduced to the app and then navigated through The Blue App follow-up user interface. The participants found the app easy to navigate and suggested some minor improvements, such as the integration of graphic design.

### Planned Research Studies to Evaluate The Blue App: Research Studies 1 and 2

The objective was to design several studies to evaluate The Blue App. In the first study (Study 1), we aim to assess whether additional comorbid conditions could be identified using The Blue App. In the second study (Study 2), we want to evaluate whether the use of The Blue App can improve outpatient compliance and treatment outcome through feedback of psychiatric symptoms.

### Design

#### Study 1

In Study 1, we want to map the prevalence of psychiatric comorbidity found in the medical records before and after the introduction of The Blue App. The hypothesis is that more diagnoses will be found in the records after the introduction of The Blue App.

#### Study 2

At discharge, eligible patients will be offered participation in a 1-year follow-up study using a randomized controlled design (Figure 1). After receiving informed consent, patients will be randomized into 3 groups and asked to answer questions regarding depressive symptoms (MADRS-S) at different time intervals over a period of 1 year after discharge. The time intervals were chosen to minimize dropout while being long enough to detect effects in the patient. We undertook a power calculation, as we found no comparable studies. Based on estimated scores on the depression rating scale (MADRS-S) at discharge, we expect scores at discharge to be around 30, with SD 7.1.

The null hypothesis for Study 2 is that no significant difference is found in the randomized controlled trial; that is, the feedback given through The Blue App would not improve the outcome or compliance. In the alternative hypothesis, we expect all patients to reduce their MARS-S scores during the study period and expect a difference of about 4 points on MADRS-S between intervention and control groups. With a power of .8, we will therefore need 3 groups of 50 patients each in order to detect differences at a 5% level.

#### Setting and Participants: Studies 1 and 2

Scania in southern Sweden has a population of over 1 million, of which 280,000 are children and adolescents. The university hospital in Malmö, the major city in the area, provides the only psychiatric emergency unit for children and adolescents, with 11 hospital beds. The hospital admits 350 unique patients annually together with a parent for acute stabilization. The most common reasons for admission are suicidal ideations, severely depressed moods, and acute crises. A majority of the patients are aged 13-17 years, with an even gender distribution.

A treatment plan is drawn up by the unit physician together with patients and parents. Nearly 15% of the patients are treated according to the Swedish Compulsory Mental Care Act. The unit team consists of physicians, psychologists, social workers, nurses, and treatment staff, often in collaboration with open-care units, schools, and social authorities. Before discharge, a rescue plan is drawn up together with patients and parents in the event of a recurrent emergency situation. Nearly 95% of the patients are discharged within a week of admission.

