**Figure 5 figure5:**
[figure not shown]
Screenshot of the MADRS-S (Montgomery-Åsberg Depression Scale) feedback screen for group 1. Source: Region Skåne.

Dropout analysis will examine for any group differences in terms of gender, age, and main International Classification of Diseases, 10th revision diagnoses. Information regarding reasons for missed appointments and dropouts will be taken from the medical records. Outcome measures are changes in MADRS-S scores and treatment compliance, as measured by attended outpatient appointments during the study period.

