### Statistical Analysis

The two studies will be analyzed separately, and baseline variables will be analyzed with descriptive statistics. Pearson’s chi-square tests will be used to determine differences between the groups in terms of gender distribution and proportion of participants scoring above cut-off in the questionnaires used.

In Study 1, we will use descriptive statistics (mean, SD, median, interquartile range, continued variables, frequency and counts, categorical variations, and exact CIs for proportions) to describe the cohort and analyze differences in the number of psychiatric diagnoses before and after the introduction (*t* test) of The Blue App [32].

In Study 2, we will analyze differences between the 3 groups in terms of changes in MADRS-S scores and treatment compliance. Outcome measures (MADRS-S scores and dropout from outpatient care) will be analyzed according to intention to treat. Linear mixed model analyses will be used to identify changes over time in depressive symptoms and to examine compliance with outpatient treatments. In these analyses, group, time, and the intercept between the groups and time will be used as fixed effects and subjects as random intercepts.

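### Study 2 ranks neither of its two outcomes and names no contrast among its three groups, so with uncorrelated outcomes its overall false-positive chance is about 9% to 23%, not 5%

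*Protocol article*

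**What the plan says.** All references are to the Protocol article.

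- **Hypothesis (Design, Study 2).** The null is that "the feedback given through The Blue App would not improve the outcome or compliance". The two outcomes are joined by an *or*.
- **Sample size (same section).** The authors "expect a difference of about 4 points on MADRS-S between intervention and control groups" and state "we expect scores at discharge to be around 30, with SD 7.1". They conclude: "With a power of .8, we will therefore need 3 groups of 50 patients each", "in order to detect differences at a 5% level".
- **Outcomes (Procedure, Study 2, after Figure 5).** "Outcome measures are changes in MADRS-S scores and treatment compliance". Neither is called primary. Compliance is measured there by attended appointments; Statistical Analysis refers instead to dropout from outpatient care.
- **Analysis (Statistical Analysis).** "we will analyze differences between the 3 groups in terms of changes in MADRS-S scores and treatment compliance". The tool is a linear mixed model with group, time and what is evidently their interaction (printed as an intercept). The section does not say which term or contrast decides the result.
- **Arms (Procedure, Study 2).** Feedback is described for group 1 only. Figure 1, which shows the three arms, is not in the text available here.

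**The concern.** A null that covers two outcomes is contradicted by a significant result on either. With three groups and no named contrast, there may also be more than one comparison per outcome. The article gives a single 5% level, attached to the sample-size statement, and sets no order among the tests. If each test is judged at 5%, then 5% is not the error rate of the hypothesis as written.

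At stake is what a positive claim would rest on. It could rest on compliance, for which no power calculation is given, or on a group comparison that does not isolate the effect of feedback. The reader could not tell from the article whether that test was meant to be decisive.

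**Working it through.** **1. Reproduce the stated sample size.** Inputs from Design, Study 2: difference 4, SD 7.1, power 0.80, level 5%. Sidedness is not stated; two-sided is tried first.

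n per group = 2 × (1.960 + 0.842)² × 7.1² / 4² = 2 × 7.85 × 50.41 / 16 = 49.5, rounded up to **50**.

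Power at 50 per group: 4 / (7.1 × √(2/50)) = 4 / 1.42 = 2.817; Φ(2.817 − 1.960) = **80.4%**. The t-based version gives 50.4 per group and 79.7% power.

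The alternatives do not reproduce 50. A one-sided 5% test needs 39. An overall three-group F test needs 47 (means 0, 0, 4 or 0, 4, 4) or 62 (means 0, 2, 4). The design is therefore sized for one unadjusted two-group comparison on MADRS-S.

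**2. False-positive chance under each reading of the plan.** Assumptions: no true difference between any groups on either outcome; each test at 5%, two-sided for contrasts; equal groups; normal test statistics. The correlation between the outcomes is not given, so it is varied. Results for comparisons that share a group come from a simulation of 1,000,000 draws.

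With uncorrelated outcomes, if one outcome gives a false positive with chance p, two give 1 − (1 − p)².

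| Tests made on each outcome | One outcome (p) | Both outcomes, uncorrelated | Multiple of 5% |
|---|---|---|---|
| One contrast, or one overall three-group test | 5.0% | 1 − 0.95² = 9.75% | 2.0 |
| Group 1 vs each other group, only results favouring group 1 counted | 4.5% | 8.9% | 1.8 |
| Group 1 vs each other group, either direction | 9.0% | 17.2% | 3.4 |
| All three pairs | 12.2% | 22.9% | 4.6 |

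Six fully independent tests would give 1 − 0.95⁶ = 26.5%, but the three pairs share groups, so 22.9% is the relevant figure.

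**3. Effect of correlation between the outcomes.**

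| Correlation | One contrast per outcome | Group 1 vs each, favouring group 1 | Group 1 vs each, either direction | All three pairs |
|---|---|---|---|---|
| 0 | 9.7% | 8.9% | 17.2% | 22.9% |
| 0.5 | 9.1% | 8.1% | 16.2% | 21.3% |
| 0.7 | 8.4% | 7.5% | 14.9% | 19.7% |
| 0.9 | 7.0% | 6.3% | 12.6% | 16.7% |

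(The 9.7% is the simulated value of the exact 9.75%.)

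**4. Can the level be split afterwards?** Keeping 80% power with a Bonferroni split over 2, 3 or 6 tests needs 60, 66 or 77 per group. At 50 per group, power for the 4-point difference falls to 72%, 66% or 57%. An ordered test of one primary contrast avoids this loss.

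**The case against.** **A stronger reading is tempting but not supported.** A reader might infer that any of three pairwise comparisons on either outcome counts as success, so that the error rate is more than four times 5%. That needs three things the article does not establish.

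- All three pairs must be tested, ungated, on both outcomes. For Study 2 the article plans mixed models and names no pairwise tests. One overall test per outcome is equally consistent with the text and gives about twice 5%.
- The comparison of group 2 with group 3 must bear on the hypothesis. The hypothesis concerns improvement through feedback, described for group 1 only. If groups 2 and 3 both lack feedback, the multiple is at most 3.4, or 1.8 if only improvement in group 1 counts.
- The correlation between the outcomes must be below about 0.65: all pairs on both outcomes give 20.6% at 0.6 and 19.7% at 0.7.

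**Other objections.** The 5% level appears only in the MADRS-S sample-size sentence, so applying it to compliance is an assumption. The power statement contrasts intervention with control groups in the plural, which fits one intervention arm and two controls; it does not show that the third arm was overlooked. Sizing each arm of a three-arm trial for a two-group contrast is ordinary practice, and the figure of 50 is correct. Testing order and adjustment may be set in an analysis plan that is not shown.

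**What of this stands.** These objections rule out a single headline multiple and any claim of a sample-size error. They do not remove the point. The article itself fixes the hypothesis, the level and the sample size, and the choice of main outcome and main contrast belongs with them in a protocol. Nor can the primary outcome be safely inferred: the power calculation points to MADRS-S, while the Study 2 aim, stated just before Design, puts compliance first.

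**Conclusion.** The point holds in a bounded form. As written, Study 2's null can be rejected on either of two unranked outcomes, with no named contrast among three groups. The sample size covers one unadjusted MADRS-S contrast only.

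With uncorrelated outcomes, every reading examined that tests both outcomes exceeds 5%: about 9% to 10% at the low end and 22.9% at the high end. Correlation reduces these figures but leaves all of them above 5% at a correlation of 0.9. Which figure applies cannot be settled, because the article does not state the tests. The range assumes that 5% is applied to each test, that compliance is analyzed as a single measure, and that no gate or adjustment is set elsewhere.

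**What to change.** State in the plan:

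1. The primary outcome is MADRS-S change, the powered outcome. It is tested at two-sided 5% in the planned mixed model, for group 1 (feedback) against one named no-feedback comparator group.
2. Compliance is tested for the same contrast, at the same level, only if the primary test is significant.
3. All other group comparisons are exploratory.

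Fixed-sequence testing is one acceptable method among several. It suits this trial because it leaves 50 per group valid, whereas splitting the level would not. The change takes a few sentences and no extra patients, and the planned MADRS-S contrast loses no power. The cost is that compliance becomes a gated secondary outcome: if the MADRS-S test fails, no confirmatory claim on compliance can be made.
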